#### Primary outcome

The severity of GAD symptoms will be measured at pre-therapy, post-therapy (16 weeks; but also after the last session in cases where the last session falls outside the range of 16 ± 2 weeks) and at 6-month follow-up, using the GAD-7 as the primary outcome measure.

The GAD-7 [33] is a seven-item self-report questionnaire assessing GAD symptoms over the preceding 2 weeks. Using the threshold score of 10, the GAD-7 has been reported to have a sensitivity of 89% and a specificity of 82% for GAD; it has also been reported as having good reliability, as well as criterion, construct, factorial, and procedural validity [33].

#### Secondary outcome measures

In addition, GAD symptoms, depression symptoms and general well-being and life functioning will be measured at pre-therapy, post-therapy (16 weeks; but also after the last session in cases where the last session falls outside the range of 16 ± 2 weeks) and at 6-month follow-up using the GADSS, PHQ-9, and CORE-OM measures, respectively. In addition, the CIPC-CSS, which is routinely administered to all CIPC clients at the end of therapy, will be administered post-therapy.

CORE-OM [35] is a 34-item questionnaire designed to measure a pan-theoretical core of clients’ global distress. The CORE-OM measures psychological distress across four domains: subjective well-being, problems or symptoms, life functioning and risk. Items refer to how respondents have been feeling over the past week and are scored on a 5-point Likert scale ranging between 0 (not at all) and 4 (most or all of the time). It has been shown to have good internal and test-retest reliability, as well as good convergent validity with other measures of psychological distress [35]. The CORE-OM is routinely used in the CIPC service, from which study participants will be recruited.

The GADSS [43] is an interview rating scale designed specifically for assessing symptom severity of GAD. Respondents are asked first to identify subjects of worry (e.g., future, health, family, finances, or work). They are then asked to rate these target worries in terms of (1) frequency of worry, (2) distress due to worry, (3) frequency of associated symptoms, (4) severity and distress of associated symptom, (5) impairment in work and (6) impairment in social function. The scale has been shown to demonstrate high internal consistency (α = 0.90), good validity and sensitivity to change in a sample of adult primary care patients [43].

The PHQ-9 [44] is a nine-item self-report instrument intended to assess the existence and severity of symptoms of depression. Internal reliability of the PHQ-9 has been reported as excellent, with Cronbach’s α of 0.89 in a primary care sample, and its strong construct validity, external validity and test-retest reliability have all been satisfactory [44].

Items 10–17 of the CIPC CSS, which is routinely administered to all CIPC clients at the end of therapy, will also be analysed. Included in these items are questions asking the client how effective counselling was in helping him or her to deal with the difficulties that led him or her to seek counselling in the first place, whether he or she felt they benefited from counselling (with prompts seeking specificity regarding how it might or might not have helped), how satisfied he or she was with the counsellor (on a range of criteria, including the capacity to adopt an approach that suited the client), and how counselling came to an end.

### Assessor training

Assessments will be conducted by a doctoral-level counselling psychologist and by psychology graduates (typically at master’s level or studying at master’s level) under the supervision of the doctoral-level psychologist. SCID-5-RV, SCID-5-PD and GADSS assessments will be audio-recorded and archived for subsequent evaluation of adherence to appropriate testing conditions. Assessors conducting post-therapy assessments will be blind to the condition the client was in.

### Sample size

A sample size of 60 participants was determined (using G*Power) [45] on the basis of the comparison between the two active treatments and pre-post within-group comparison. We used a minimum meaningful comparison (moderate effect size; *f* = 0.25) that is used in assessing difference between two treatments (cf. Shapiro [46]), with statistical power of 0.80 and alpha level of 0.05.

We expect that the study is likely to detect change over time within the two active treatments (the pre-post change should be large). It is envisaged, however, that the sample size may be too small to find any difference between the active treatments (often the differences between active treatments are rather small). Because the present project is a feasibility study, exploratory use of the initial comparison data should help in planning a definite non-inferiority trial that could be developed as phase 2 of the present study, with further participants recruited to the two active interventions on the basis of an estimate of the numbers needed to determine definite evaluation.

Practically speaking, there should be a sufficient number of referrals. Annual referral numbers for CIPC Dublin North-East, where the study is hosted, is estimated at approximately 2000 clients, with at least 25% of individuals referred for anxiety problems. Because we will be recruiting over a 2-year period, we anticipate no issue with recruiting 60+ participants from a prospective pool of 1000 clients.

### Data management

All identifying paper data (i.e., signed consent forms, forms listing participant codes) will be stored in a locked file cabinet in a locked room in the School of Psychology, TCD. Each potential participant assessed by the research team will be given a unique study code which identifies the client as assessed for the study. In addition, participants who proceed from assessment to the trial will be given a unique trial code. This code will identify the client and the corresponding therapist. Paper copies of measures will be identifiable only by the study and/or trial codes. All regulations set by the ethics committees (the Research Ethics Committee at the School of Psychology, TCD, and the Research Ethics Committee, HSE, North East) as well as data protection regulations will be observed. Electronic data will be routinely cross-checked to mitigate against data entry errors, with all data double-entered into two parallel data sets, which will be routinely compared. Multiple imputation will be used for missing data. Data-monitoring oversight will be provided by [name], a health psychologist and statistician with no direct allegiance to either of the two compared approaches and who will address any issues arising with the principal investigator (PI) as well as reporting directly to the trial management group (TMG) and trial steering committee (TSC) (*see below*).

### Statistical methods

The main analysis will be performed under the direction of [name]. The main analysis will be run as intention-to-treat analysis (within- and between-group comparisons at 16 weeks, the end of treatment, and at 6-month follow-up) as well as per-protocol analysis (which will exclude participants that had fewer than eight sessions; i.e., half of the expected length of the treatment).

Primary (GAD-7) and secondary (GADSS, PHQ-9 and CORE) outcomes will be analysed using repeated-measures analysis of variance for the two active conditions at the end of treatment, at 16 weeks, and at the 6-month follow-up. Analyses will be based on the intention-to-treat sample. Effects will be tested at the 0.05 level. The magnitude of the within-group effects of each of the interventions (Cohen’s *d*) will be calculated. The magnitude of between-group effects will be established as well. Analysis will also be conducted to determine the proportion of participants who evinced clinically significant change and reliable improvement [47] at the end of the treatment, at 16 weeks, and at 6-month follow-up for the two active treatments on the GAD-7.

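### The between-arm GAD-7 analysis names no baseline covariate although pre-therapy GAD-7 is collected; this costs precision on either reading of the repeated-measures ANOVA

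*Protocol article*

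**What the plan says.** Under Statistical methods, the protocol article states: "Primary (GAD-7) and secondary (GADSS, PHQ-9 and CORE) outcomes will be analysed using repeated-measures analysis of variance". With its occasions, the method reads "repeated-measures analysis of variance for the two active conditions at the end of treatment, at 16 weeks, and at the 6-month follow-up". No covariate is named there, and baseline adjustment is not mentioned elsewhere in the article.

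The baseline score will exist. Under Primary outcome: "The severity of GAD symptoms will be measured at pre-therapy, post-therapy (16 weeks", followed by the 6-month follow-up, "using the GAD-7 as the primary outcome measure".

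Three other statements bear on the reading:

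- Statistical methods also promises within-group comparisons and within-group Cohen's d, and Sample size refers to a pre-post comparison within groups. Both suggest that pre-therapy scores enter somewhere.
- Data management says "Multiple imputation will be used for missing data".
- Patient consent process and assessment, and Primary outcome, schedule assessments at 16 weeks and 6 months later (week 42). A separate end-of-therapy assessment takes place only when therapy finishes outside 16 ± 2 weeks.

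**The concern.** The article names the model and its occasions, so this is a stated choice and not a detail left to an unseen analysis plan. The text allows two readings, and neither uses baseline efficiently.

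- **Post-randomisation occasions only.** The pre-therapy score plays no part in the comparison of arms.
- **Pre-therapy as a level of time.** The group-by-time contrast subtracts baseline with a fixed weight of one. The group main effect averages in an occasion at which no treatment effect can exist.

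The trial is small. The article says that 60 may be too few to find a difference between active treatments, and it gives comparative estimates for planning a non-inferiority trial as one purpose of the study. Those estimates would be noisier than the collected data require.

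**Working it through.** **The plan's own figure.** Sample size states "A sample size of 60 participants was determined (using G*Power" and gives "moderate effect size; *f* = 0.25", power 0.80 and alpha 0.05. For two groups d = 2f = 0.5. A one-way F test with these inputs needs 128 in total, and 60 gives power 0.48. A repeated-measures between-group test comes near 60 only with settings that the article does not state (three measurements with correlation 0.2, or four with 0.3, each give 62). So 60 cannot be reproduced from the stated inputs, but it is not shown to be wrong, and nothing below depends on it.

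**Inputs.** N = 60 and d = 0.5 come from Sample size. Equal arms of 30 are assumed. A common correlation r between any two occasions, with equal SDs and a constant effect, is assumed at 0.3, 0.5 and 0.6, because the article gives none.

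**Method.** Noncentral F with 1 numerator df and noncentrality λ = (N d² / 4) / V = 3.75 / V. V is the variance relative to a single unadjusted score. Denominator df are 58, or 57 with a covariate.

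**One post-treatment occasion.** V = 1 unadjusted, 2(1 − r) for change scores, 1 − r² with baseline as covariate.

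| r | Unadjusted: V, power | Change: V, power | Adjusted: V, power |
|---|---|---|---|
| 0.3 | 1, 0.48 | 1.40, 0.36 | 0.91, 0.51 |
| 0.5 | 1, 0.48 | 1.00, 0.48 | 0.75, 0.59 |
| 0.6 | 1, 0.48 | 0.80, 0.57 | 0.64, 0.66 |

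The ratio of adjusted to change-score variance is (1 − r²) / [2(1 − r)] = (1 + r)/2, which is below 1 for every r below 1. For r below 0.5, change scores are less precise than ignoring baseline.

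**Mean of weeks 16 and 42.** This is closer to what a repeated-measures group test does. V = (1 + r)/2 unadjusted, (1 + r)/2 + 1 − 2r for change from baseline, (1 + r)/2 − r² adjusted.

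| r | Unadjusted: V, power | Change: V, power | Adjusted: V, power |
|---|---|---|---|
| 0.3 | 0.65, 0.66 | 1.05, 0.46 | 0.56, 0.72 |
| 0.5 | 0.75, 0.59 | 0.75, 0.59 | 0.50, 0.77 |
| 0.6 | 0.80, 0.57 | 0.60, 0.69 | 0.44, 0.82 |

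**Dilution of the main effect.** With pre-therapy, week 16 and week 42 as three levels, the expected group difference is (0 + 0.5 + 0.5)/3 = 0.33. The variance of the mean is (1 + 2r)/3, so λ = 3.75 × (2/3)² / [(1 + 2r)/3] = 3.13 / 2.50 / 2.27, and power is 0.41 / 0.34 / 0.32.

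**Width of the confidence interval.** This does not depend on d. Adjusted against unadjusted, the ratio of standard errors at one occasion is √(1 − r²) = 0.95 / 0.87 / 0.80. For the two-occasion mean it is √(0.56/0.65), √(0.50/0.75), √(0.44/0.80) = 0.93 / 0.82 / 0.74.

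**The case against.** **Pre-therapy is probably a level of time.** The promised within-group comparisons suggest it. On that reading the group-by-time test does remove baseline differences. A reader might infer that nothing in the plan corrects for a chance imbalance (standard error √(2/30) = 0.26 SD at 30 per arm). The article does not support so strong a statement. What stands is that a change score is a less efficient correction than a covariate.

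**A single-occasion test is not the planned analysis.** This is right: 0.48 understates the power of a repeated-measures group test. Taking the three listed occasions at face value, V = (1 + 2r)/3 and unadjusted power is 0.74 / 0.65 / 0.60. The gain survives on that comparator too: subtracting r² from V gives 0.82 / 0.84 / 0.88. Those three-occasion figures are optimistic, since most participants may have no separate end-of-treatment assessment.

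**The correlation is unknown and may be low.** Entry requires a GAD-7 of at least 11, which restricts the baseline range. At r = 0.3 the gain is small. This stands.

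**d = 0.5 is generous.** The Discussion cites typical differences of 0 to 0.2. At d = 0.2, single-occasion power is 0.12 unadjusted and 0.13 / 0.14 / 0.16 adjusted, so adjustment will not make the trial a powered comparison. The narrower interval remains, and it is what matters for planning.

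**Two further inferences do not hold.** A reader might say that repeated-measures ANOVA will discard incomplete cases, but the article specifies multiple imputation. A reader might also call allocation unrestricted. Randomisation describes a separate random sequence for each therapist and does not say whether it is blocked.

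**Conclusion.** The point holds as a loss of precision. The article specifies repeated-measures ANOVA on post-randomisation occasions and names no baseline covariate, and on either reading the between-arm estimate is less precise than the collected data allow. For the arm effect averaged over weeks 16 and 42, baseline adjustment raises power at d = 0.5 from 0.66 / 0.59 / 0.57 to 0.72 / 0.77 / 0.82 at r = 0.3 / 0.5 / 0.6. These figures rest on equal arms, equal SDs, a constant effect and a correlation that the article does not supply; the entry threshold may place it at the low end.

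A reader might infer that the planned test is invalid or biased. It is not: under randomisation both forms are unbiased tests of no arm difference. If pre-therapy is a level of time, the group main effect does average in a zero, so it should not be reported as the treatment effect.

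**What to change.** State whether pre-therapy GAD-7 enters the model, and make it a covariate:

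- Estimate the between-arm GAD-7 difference in a linear mixed model (or ANCOVA) on weeks 16 and 42, the two occasions scheduled for everyone, with pre-therapy GAD-7, arm, time and arm-by-time.
- Report the adjusted week-16 difference with its 95% CI.
- Analyse the end-of-treatment score separately with the same baseline adjustment, because a distinct assessment exists only for participants who finish outside 16 ± 2 weeks.
- Use the same form for GADSS, PHQ-9 and CORE-OM, each with its own baseline.

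The within-group effect sizes can stay as planned. The cost is a change of wording in Statistical methods; no additional data or visits are needed.

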## Discussion

NICE recommends that GAD be treated with medication and/or psychological treatment, which is currently limited to various forms of CBTs [10]. Although the efficacy of CBTs is relatively well studied, questions remain about their relative efficacy and about the possibility of alternative psychological therapies [14]. Increasing treatment options appears to be desirable [16]. The present study aims to contribute to all these goals. Furthermore, there is the possibility that the study may point to the differential effects of different psychological treatments.

Specifically, the present project should further contribute to the exploration of EFT as a viable treatment for GAD. By providing first-comparison data, the present study should also contribute to the exploration of EFT as an alternative to CBT in the treatment of GAD. As a feasibility study, it should contribute to the planning of a definitive non-inferiority trial that would establish EFT’s relative efficacy in comparison to CBT as an established treatment. Given that the host of the study, the HSE’s CIPC service, is a national service employing 280 therapists and seeing several thousand clients each year, there is a clear opportunity for the present study to evolve naturally into a definitive study.

Psychotherapy research studies often show equivalence [48] with differences often in the range of 0 to 0.2 of Cohen’s *d* [49]. If findings from the present study indicate that EFT is comparable to CBT using typical psychotherapy research standards, a non-inferiority study may be a natural next step. Depending on the results of this feasibility study, we should also be able to assess the practical issues involved in running such a design with the CIPC service. We should also be able to estimate the sample size needed to run such a project.

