EFT [20, 21] is a research-informed therapy that focuses on (1) increasing awareness of adaptive and maladaptive emotions, (2) enhancing emotion regulation, (3) transforming maladaptive emotions and (4) reflecting on adaptive emotions [22]. EFT is an empirically supported treatment for major depressive disorder [17, 23] and is also extensively studied for complex trauma [24]. In comparison with CBT for depression, EFT showed comparable results with a slight advantage for EFT in the domain of interpersonal functioning [17]. EFT is also currently being adapted for other mental health disorders, such as social anxiety, where the central problems lie in maladaptive emotional processing [25–28]. Because GAD is understood to be caused by difficulties in emotional processing (e.g., an incapacity to tolerate difficult emotions, combined with a tendency to avoid such difficult emotions) [11, 29], a therapy such as EFT that focuses on the processing and transformation of painful emotions is theoretically a good match for GAD difficulties [18]. Furthermore, EFT also focuses on the overcoming of emotional avoidance, a central feature of GAD.

A group of researchers, led by the lead author of the present article, developed EFT for GAD [18, 19] and tested it in an open trial with promising results [30]. The present project should further contribute to the exploration of EFT as a viable alternative to CBT in the treatment of GAD. The feasibility study should establish the relative efficacy of EFT in comparison to CBT as an established treatment.

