### Objectives

The overall aim of the project is to contribute to the planning of a definitive non-inferiority trial that would establish the relative efficacy of EFT in comparison to CBT as an established treatment. The present project will provide first-comparison data that, if suggesting comparable or better outcomes, should help to plan a definitive non-inferiority trial. It will test recruitment, adherence, and retention rates, as well as provide estimates of comparative outcomes that can be used to inform power calculations for a definitive non-inferiority trial.

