### Randomisation

Because the organisational structure of CIPC means that it would not always be possible to randomise between therapists (e.g., often only one therapist works in a particular location), the decision was made to randomise within therapists. [name], a member of the research team with no allegiance to either intervention and no involvement in the delivery of either training or supervision, will generate the allocation sequence using an online randomiser. A random sequence (of numbers 1 and 2, corresponding to EFT or CBT) will be generated for each therapist, who will be identified by code and not by name. After SCID-5 assessment (*see below*), and after allocation to a therapist (*see* the next section on patient consent process and assessment), a member of the research team (the trial manager) will contact [name] and request the assignment (either EFT or CBT) for the next participant for the therapist in question.

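### The Background says this 60-person feasibility trial should establish EFT's efficacy relative to CBT, and the next step hangs on EFT looking comparable, a term with no criterion that 30 per arm could not support

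*Protocol article*

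**What the plan says.** All references are to the protocol article.

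- **Background**, last paragraph: "The feasibility study should establish the relative efficacy of EFT in comparison to CBT as an established treatment".
- **Objectives**: establishing relative efficacy belongs to a definitive non-inferiority trial. The present data, "if suggesting comparable or better outcomes, should help to plan a definitive non-inferiority trial". Recruitment, adherence and retention are what this trial will test, and it will supply estimates for later power calculations.
- **Sample size**: "A sample size of 60 participants was determined", and "We used a minimum meaningful comparison (moderate effect size; *f* = 0.25"), "with statistical power of 0.80 and alpha level of 0.05". The next paragraph warns that the sample may not suffice to find a difference between the two active arms and calls the use of the comparison data exploratory.
- **Statistical methods**: repeated-measures analysis of variance; "Effects will be tested at the 0.05 level". Between-group effect magnitudes are to be established, and the proportions with clinically significant change and reliable improvement on the GAD-7 reported. The section names no interval and no margin.
- **Discussion**: the condition is worded "If findings from the present study indicate that EFT is comparable to CBT using typical psychotherapy research standards"; the consequence offered, tentatively, is that the later trial could come next. The preceding sentence mentions differences of 0 to 0.2 in Cohen's d as what psychotherapy research often finds.

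**The concern.** There are two linked faults.

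First, the Background gives this trial a task that three other sections say it does not have or may be unable to perform. That is a contradiction in the article's own text, not a detail left to another document.

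Second, the condition for moving on is worded as an outcome result (comparable, or comparable or better), and nothing says how it will be judged. The Statistical methods section describes tools for detecting a difference. Neither a non-significant test nor an effect size without its interval shows that two treatments are similar. Having said that a difference may well go undetected, the plan should say what an undetected difference will and will not be taken to mean. Otherwise the expected null result could be reported as comparability with an established therapy while the data remain compatible with a deficit that the plan itself calls meaningful.

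**Working it through.** **The contradiction, side by side**

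| Section | Who establishes relative efficacy? |
|---|---|
| Background | this feasibility study |
| Objectives | the definitive trial; this one helps to plan it |
| Sample size | this trial may be too small to find any between-arm difference |
| Discussion | the definitive trial |

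The Background sentence is the odd one out.

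**Inputs.** N = 60, f = 0.25, power 0.80 and alpha 0.05 (Sample size); tests at 0.05 (Statistical methods). Assumed: 30 per arm, because the Randomisation section says only that "A random sequence (of numbers 1 and 2, corresponding to EFT or CBT) will be generated for each therapist" and gives no ratio; a two-sided test; equal SDs; no therapist effect. Differences are in SD units. For two groups d = 2f = 2 × 0.25 = 0.50.

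**The plan's own figure.** The stated inputs neither confirm nor refute N = 60, because the test, the number of visits and the correlation between visits are not given. At f = 0.25, 80% power and alpha 0.05:
- a plain two-group comparison needs N = 128;
- a repeated-measures between-group test at correlation 0.5 needs 98, 86 or 82 for 2, 3 or 4 visits;
- a repeated-measures within-subject or interaction test at correlation 0.5 needs 34, 28 or 24.

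The point below does not depend on which was used.

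**Precision at 30 per arm, single unadjusted comparison**
- SE(d) = √(2/30) = 0.258.
- 95% half-width = t(0.975, 58) × SE = 2.002 × 0.258 = 0.517.
- An observed difference of 0 therefore has an interval of about −0.52 to +0.52, which contains −0.50.

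Adjusting for baseline with correlation r multiplies the SE by √(1 − r²). At r = 0.5 the SE is 0.258 × 0.866 = 0.224 and the half-width about 0.45. At r = 0.7 the SE is 0.258 × 0.714 = 0.184 and the half-width about 0.37. With 24 per arm (20% loss, assumed) and no adjustment the SE is √(2/24) = 0.289 and the half-width about 0.58.

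**If comparable were read as non-significant.** Chance that the test fails to show EFT worse, from the noncentral t with noncentrality d/SE:

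| True deficit of EFT | 30 per arm, r = 0 | 30 per arm, r = 0.5 | 30 per arm, r = 0.7 | 24 per arm, r = 0 |
|---|---|---|---|---|
| 0.3 SD | 79% | 74% | 64% | 83% |
| 0.4 SD | 67% | 58% | 43% | 73% |
| 0.5 SD | 52% | 41% | 24% | 60% |

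**If comparable were read as an observed deficit below 0.2.** Chance of passing = Φ((0.2 − d)/0.258), at 30 per arm, r = 0:
- true deficit 0.3: Φ(−0.387) = 35%
- true deficit 0.5: Φ(−1.162) = 12%
- no true deficit: Φ(0.775) = 78%, so 22% of trials of an equal therapy would fail.

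The two readings give very different answers from the same data.

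**The case against.** A reader might infer that comparability will be decided by the 0.05 test and a point estimate, and that such a rule would usually miss an EFT truly worse by 0.3 to 0.5 SD. The article does not support this. It does not say that non-significance will be read as comparability, and it gives d of 0 to 0.2 as background, not as a threshold. The arithmetic does not bear out the general claim either. Usually missing a deficit is right at 0.3 SD under a non-significance reading. At 0.5 SD that reading is close to even, and with baseline adjustment the deficit is missed less often than not. A point-estimate rule at 0.2 would catch most such deficits.

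Four further points stand.
- The consequence is tentative: a next trial may follow. No non-inferiority conclusion is planned here, and no rule abandons EFT if it looks worse.
- The low power is disclosed and the comparison is called exploratory.
- Feasibility is not ignored. The Discussion says directly afterwards that practical issues will be assessed, and recruitment, adherence and retention are stated aims.
- Numerical progression criteria may reasonably sit in a fuller protocol or analysis plan that is not shown.

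None of this removes the contradiction in the Background. Nor does it supply a meaning for the term on which the article itself hangs the next step. The disclosed low power makes it more important to say what a null result will mean.

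**Conclusion.** The point holds in a limited form. The Background sentence conflicts with the Objectives, Sample size and Discussion sections and should be corrected. The comparability condition has no criterion, and a trial of this size could not support a conclusion of comparability: the 95% interval is about ±0.52 SD unadjusted, as wide as the plan's own minimum meaningful effect of d = 0.5. With baseline adjustment and full retention it narrows to about ±0.45 (r = 0.5) or ±0.37 (r = 0.7). An observed zero would then just exclude 0.5 SD but still leave a deficit of 0.3 SD open.

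The 79% and 52% figures (74% and 41% at r = 0.5) apply only if non-significance is taken as comparability. They show what the wording leaves open, not what the trial has said it will do. They rest on 1:1 allocation, a two-sided 0.05 test of a single comparison, equal SDs, no therapist effect and no dropout.

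**What to change.** 1. In the Background, say that the study should give a first estimate of the relative efficacy of EFT.
2. State in the Objectives and Discussion that no conclusion of comparability or non-inferiority will be drawn from this trial, and that a non-significant test will not be read as comparability.
3. In Statistical methods, make the between-arm GAD-7 difference with its 95% confidence interval the between-arm result.
4. Base the decision to proceed mainly on the declared feasibility aims (recruitment, adherence, retention), and use the interval to inform planning of the definitive trial.

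A veto that applies only when the whole 95% interval lies beyond a fixed deficit is not a useful addition. Set at 0.2 SD, it would require an observed deficit above 0.2 + 0.517 = 0.717. About 80% of trials with a true deficit of 0.5 SD, and 95% with 0.3 SD, would pass it.

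The cost is wording and reporting only, with no extra participants or data. The downside is a more modest headline claim.
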